## 2. Materials and Methods

### 2.1. Study Design

This prospective, unicentric, double-blind, randomized, and placebo-controlled trial is being performed by a multidisciplinary team of researchers from the Food Bioactive Amines and Polyamines research group at the Food and Nutrition Campus, University of Barcelona, and the Cardiovascular Risk, Nutrition, and Aging research group at the August Pi i Sunyer Biomedical Research Institute (IDIBAPS) of the Hospital Clínic de Barcelona. The study commenced in June 2022 and is expected to conclude in May 2025.

The study design is outlined in Figure 2. In this protocol, participants are randomized into eight study groups (50 individuals/group), based on combinations of diet (low-histamine or control diet) and supplementation (placebo, porcine DAO, and two different doses of plant-based DAO). The intervention period lasts three months.

The sample size is calculated considering the average number of symptoms reported by histamine-intolerant patients and the standard deviation (11.1 symptoms/patient ± 4.8) [6]. To detect a variation in at least two symptoms per patient, assuming an alpha risk of 0.05 and a beta risk of 0.02 in a bilateral contrast, a minimum of 42 participants per group is required. To accommodate a 10% drop-out rate, 50 participants will be recruited for each group. Therefore, as the study includes eight intervention groups, the total number of participants is 400.

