### 2.2. Study Outcomes

#### 2.2.1. Symptoms of Histamine Intolerance

Symptoms related to histamine intolerance, listed in Figure 1, are evaluated through specific validated questionnaires as follows: (a) gastrointestinal manifestations are assessed by the Gastrointestinal Quality of Life Index (GIQLI) and Bristol Stool Scale [38,39]; (b) headaches by the Migraine Disability Assessment Scale (MIDAS) and Headache Impact Test (HIT-6) [40,41]; (c) respiratory symptoms by the Rhinoconjunctivitis Quality of Life Questionnaire (RQLQ) and Nasosinusual Symptoms Questionnaire (SNOT-22); and (d) dermatological manifestations by SCORing Atopic Dermatitis (SCORAD), the Itch Severity Scale (ISS), Quality of Life Index for Atopic Dermatitis (QoLIAD), and Dermatology Life Quality Index (DLQI) [42,43,44,45,46]. Additionally, the general quality of life of patients is assessed using the SF-36 Health Questionnaire [47].

Data obtained from these questionnaires will be used to evaluate the effectiveness of the dietary treatment in the improvement or remission of patient symptomatology. Differences among the study groups will be determined using covariance analysis with baseline parameters as covariates. A multivariate analysis adjusted for age, sex, and clinical parameters with significant baseline differences among groups will also be applied. These differences will be expressed as means (95% confidence intervals).

All collected data regarding symptomatology will also be used to assess potential correlations with other study outcomes, such the composition of intestinal microbiota, the urinary profile of histamine metabolites, serum DAO activity, plasma histamine levels, and DAO-encoding gene variants.

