## 3. Discussion

The study described here is the first prospective, unicentric, double-blind, randomized, and placebo-controlled trial designed to evaluate the efficacy of combining a low-histamine diet with DAO supplementation in alleviating symptoms of histamine intolerance. Previous intervention studies have reported positive outcomes for either the low-histamine diet or DAO supplementation, although most of them have certain limitations regarding the number of patients, follow-up period, and control group [11,12,13,14,15,16,17,18,19,20,21,22,23,24,25,26,27,28,29,30,31]. In this sense, the broad majority of these studies (18 out of 21) considered small patient cohorts (fewer than 56 participants), 61% of which did not even exceed 30 patients. Although the studies conducted by Sienbenhaar et al. (2016) and Cucca et al. (2022) included larger sample sizes (157 and 146 patients, respectively), both trials entailed a significant drawback, due to the absence of a control group in their design [20,24]. In fact, the lack of a control group (i.e., not following a low-histamine diet or receiving placebo supplementation) is a recurring limitation in many of these studies (16 out of 21). Only the work performed by Izquierdo-Casas et al. (2019) included a cohort of 100 patients diagnosed with headache and DAO deficiency, with 50% receiving porcine DAO supplementation and the other half receiving a placebo [30]. Regarding the duration of the intervention, most of the studies, with the exception of three [13,18,22], were limited to a maximum of 4 weeks. For example, Mušič et al. (2013) considered a longer dietary intervention period of up to 12 months, during which patients with DAO deficiency followed a low-histamine diet. However, only 20 patients were monitored, and there was a lack of a control group [18]. The current study aims to address all these limitations by involving a total of 400 patients, including a placebo-controlled group and an intervention period of 3 months. The study design, with distinct intervention groups following a low-histamine diet and/or receiving DAO supplementation, will allow for the assessment of the impact of each treatment separately, as well as potential synergistic effects. Additionally, this clinical trial is pioneering in its evaluation of DAO sourced from plants as a dietary supplement for managing histamine intolerance.

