This study is also designed to provide valuable insights into the prevalence of genetic polymorphisms and levels of DAO activity and plasma histamine in patients with histamine intolerance. These parameters are correlated with the presence, intensity, and evolution of symptoms throughout the dietary intervention. In general, the results of this study should help to improve dietary recommendations for histamine-intolerant patients and ultimately enhance their quality of life.

The primary limitation of this study is that, despite the expected high number of participants (n = 400), the randomization into multiple intervention groups (low-histamine diet versus control, animal- and plant-based supplementation, and two dosage levels of the latter) results in a smaller sample size per group, which could potentially reduce the statistical power of the analyses. To address this, secondary analyses combining specific intervention groups, when methodologically appropriate, can be performed to effectively increase the sample size in those comparisons. Another limitation could be that the unicentric design means findings may not be generalizable to other histamine-intolerant populations and could be subject to selection bias among patients with this food intolerance. Finally, the reliability of dietary records may be influenced by recall bias or social desirability bias.

The main strength of the study is its design as a randomized clinical trial, which allows causal inference. Standardized data collection conditions for anthropometric and blood measurements, as well as for symptom recording and dietary intake frequency using validated questionnaires, are additional strengths. Overall, the findings of this clinical trial will contribute to the development of more effective and tailored dietary interventions for histamine intolerance. Specifically, robust and reliable evidence will be generated regarding the efficacy of the low-histamine diet, the current gold-standard treatment. Furthermore, the study will clarify the role of supplementation in symptom management, including the optimal type and dosage, thereby providing evidence-based recommendations for its use in clinical practice.

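### A 2 × 4 factorial is sized per cell and described as a comparison of groups, with pooling optional and unnamed; the promised synergy assessment has about 29% to 40% power

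*Protocol article*

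**What the plan says.** Protocol article, 2.1 Study Design: "participants are randomized into eight study groups (50 individuals/group), based on combinations of diet (low-histamine or control diet) and supplementation". Section 2.1.2 has each participant draw one envelope for diet and another for supplement, so both factors are randomised for everyone.

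The sample size in 2.1 is set per cell. It takes a symptom count of "11.1 symptoms/patient ± 4.8" and states its target as "To detect a variation in at least two symptoms per patient". The error rates are given as "assuming an alpha risk of 0.05 and a beta risk of 0.02 in a bilateral contrast". The article's conclusion from these inputs is that "a minimum of 42 participants per group is required". That is raised to 50 for drop-out and multiplied by eight to give 400.

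For symptoms, section 2.2.1 says: "Differences among the study groups will be determined using covariance analysis with baseline parameters as covariates". A further version adjusts for age, sex and clinical parameters that differ at baseline. No factor, contrast or interaction is named.

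The Abstract expects the comparison of the groups to show individual effects and possible synergy. The Discussion says the design "will allow for the assessment of the impact of each treatment separately, as well as potential synergistic effects". It later gives the small groups, and the power they may cost, as the main limitation, and answers that with: "secondary analyses combining specific intervention groups, when methodologically appropriate, can be performed to effectively increase the sample size in those comparisons".

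**The concern.** In a factorial trial each participant counts towards both questions. The diet effect can be estimated from all 400 and each supplement effect from about 200. The article presents the eight small groups as a loss of power and offers pooling as an optional remedy. Read together, 2.1, 2.2.1 and the Discussion point to an analysis led by cell comparisons, in which the margins come second if they come at all.

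Three things are at stake:

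- Cell comparisons at the planned size have roughly even odds of detecting the effect that the trial was sized for.
- There are many ways to merge four supplement levels, two of which are doses of one product. With no named groups and no rule beyond appropriateness, the choice of merge stays open.
- Synergy is a difference of differences. A favourable mean in one combined cell does not show it, and the interaction contrast is the least precise one in the design.

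**Working it through.** **Inputs.** From 2.1: effect 2 symptoms, SD 4.8, two-sided alpha 0.05, 50 per cell, 10% loss. Evaluable per cell: 50 × 0.9 = 45. The powers are unadjusted, because the article gives no correlation between baseline and follow-up.

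**The plan's own figure.** Normal approximation for two means: n per group = 2 × [(1.960 + z) × 4.8 / 2]².

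- Beta 0.02 (z = 2.054): 186 per group.
- Beta 0.20 (z = 0.842): 91 per group.

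The stated 42 is not reproduced either way. That is a separate defect; here it only means that 42 to 50 per cell cannot be taken as adequate for cell contrasts.

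**Cells and margins.** SE = 4.8 × √(1/n₁ + 1/n₂); power for a difference of 2 from the two-sample t test.

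| Contrast | n₁ v n₂ | SE | Power |
|---|---|---|---|
| One cell v another | 45 v 45 | 1.012 | 50% |
| Each supplement v placebo, over both diets | 90 v 90 | 0.716 | 79% |
| Low-histamine v habitual diet, over all supplements | 180 v 180 | 0.506 | 98% |

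With Bonferroni for three supplement contrasts (alpha 0.0167), the supplement margin has 65% and the cell contrast 33%. Across 42 to 50 evaluable per cell, the unadjusted-alpha ranges are 47% to 54% (cell), 77% to 83% (supplement margin) and 97% to 99% (diet margin).

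**Omnibus test.** An eight-group F test on 7 and 352 df, with a 2-symptom diet effect at every supplement level, has 83% power, against 98% for the direct diet contrast.

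**Synergy** (normal approximation).

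- One supplement v placebo, by diet (four cells): SE = 4.8 × √(4/45) = 1.431. Power for a 2-symptom interaction is 29%. Detectable at 80% power: 1.431 × (1.960 + 0.842) = 4.0 symptoms.
- Any DAO v placebo, by diet: SE = 4.8 × √(2/135 + 2/45) = 1.168. Power is 40%; detectable 3.3 symptoms.

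Over 42 to 50 per cell these powers are 27% to 31% and 38% to 44%.

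**When the supplement margin stops helping.** Assume, for illustration, an effect of 2 on the habitual diet and x on the low-histamine diet.

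- The marginal effect is (2 + x)/2. With x = 0 it is 1 symptom, and power at 90 v 90 is 28%, below the 50% of the cell contrast on the habitual diet.
- The marginal SE is 1.012/√2, so the margin does better only when (2 + x)/2 exceeds 2/√2 = 1.41, that is, when x exceeds about 0.83.

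**The case against.** **The eight-group reading is inferred.** Section 2.2.1 does not specify a one-way model. The Abstract uses the word group both for the two diet arms and for the eight combinations, and a covariance analysis can hold both factors. This stands as a limit on certainty. The inference is still strong, because the sample size is per cell and the Discussion gives pooling secondary status; if the margins were the main analysis, pooling would already be primary.

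**Interaction terms may sit in a fuller document.** This stands. A reader might infer that the trial has no test of synergy, or that an eight-group analysis cannot provide one. The article supports neither. Eight cell means contain the interaction as contrasts, and the model may be written elsewhere. What the article does fix is the promise of synergy and the sample size behind it.

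**The loss can be overstated.** A reader might infer that most of the power is discarded. The figures do not show that: 98% falls to 50% for diet and 79% to 50% for each supplement in cell contrasts, and the omnibus test keeps 83% for diet. Nor do the margins remove the power problem, with 65% per supplement after Bonferroni. The limitation in the Discussion is partly fair.

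**Margins are not a free gain.** This stands. The Introduction says supplements act on dietary histamine, which the diet removes, so a smaller supplement effect on the low-histamine diet is plausible. A main model with additive terms only would be a poor choice.

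**The powers concern symptom counts without adjustment, whereas 2.2.1 analyses questionnaire data with baseline covariates.** This stands too. Adjustment would raise every power by an unknown amount.

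Finally, a reader might infer that pooling is meant to be chosen after the data are seen. The text does not say so; it only fails to rule it out.

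**Conclusion.** The concern holds in this form. The trial randomises a 2 × 4 factorial, is sized per cell, describes its analysis as differences among groups, and leaves pooling optional and unnamed. At the protocol's effect and SD, naming the marginal contrasts as the main ones moves power from about 50% to 98% for diet and to 79% for each supplement (65% after Bonferroni). The synergy aim has 29% to 40% power for a 2-symptom interaction, and only the general remark on small groups hints at that.

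These figures assume 45 evaluable per cell, SD 4.8, no baseline adjustment and, for the margins, roughly additive effects. That cell contrasts lead the analysis is a strong inference, not stated text. The point should be acted on, but it does not invalidate the design.

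**What to change.** In the baseline-adjusted ANCOVA of section 2.2.1:

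1. Prespecify terms for diet (two levels), supplement (four levels) and diet × supplement.
2. Name the main contrasts: low-histamine v habitual diet averaged over supplements, and each active supplement v placebo averaged over diets, with Holm or Dunnett for the three.
3. Report the interaction contrasts with 95% CIs as the only basis for a synergy statement, and declare them low-powered. Carry that caveat into the Abstract and Discussion.
4. Report the simple effects within each diet alongside the margins.
5. Replace the optional-pooling sentence in the Discussion with these named contrasts.

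The cost is wording in the protocol and analysis plan; no participants, visits or measurements are added. The drawback is that a margin averages over the other factor and loses power if the supplement effect differs strongly by diet, which is why steps 1, 3 and 4 belong together.

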## Figures and Tables

**Figure 1 nutrients-17-00029-f001:**
[figure not shown]
Main symptoms of histamine intolerance and the corresponding histamine receptors [1,4,9].

**Figure 2 nutrients-17-00029-f002:**
[figure not shown]
Schematic representation of the study design.

## Data Availability

The original contributions presented in the study are included in the article; further inquiries can be directed to the corresponding authors.

## Abbreviations

DAO	Diamine Oxidase;
FFQ	Food Frequency Questionnaire;
PCR	Polymerase Chain Reaction;
EDTA	Ethylenediaminetetraacetic acid;
BP	Blood Pressure;
GIQLI	Gastrointestinal Quality of Life Index;
MIDAS	Migraine Disability Assessment Scale;
HIT-6	Headache Impact Test;
RQLQ	Rhinoconjunctivitis Quality of Life Questionnaire;
SNOT-22	Nasosinusual Symptoms Questionnaire;
SCORAD	SCORing Atopic Dermatitis;
ISS	Itch Severity Scale;
QoLIAD	Quality of Life Index for Atopic Dermatitis;
DLQI	Dermatology Life Quality Index;
LC-ESI-MS/MS	Liquid Chromatography-Electrospray Ionization-Tandem Mass Spectrometry;
HPLC-TOF-MS	High-Performance Liquid Chromatography-Time-of-Flight Mass Spectrometry;
MAIT	Metabolite Automatic Identification Toolkit
PLS-DA	Partial Least Squares Discriminant Analysis
